**Table 3. Evaluation outcomes**

| **Objective** | **Primary Outcome** | **Secondary outcomes** |
| --- | --- | --- |
| Fast track ART initiation counseling (Objective 1) | Proportion of patients who initiate ART within 30 days of becoming ART eligible (S) and the proportion of patients who are alive, in care, and virally suppressed (< 400 copies/ml^3^) within nine months of ART eligibility (L). | Proportion of patients who initiate ART within one week of becoming ART eligible  Demographic and clinical characteristics of patients who do and do not achieve primary outcomes (age, sex, baseline CD4 counts, TB diagnosis, other characteristics as allowed by data). |
| Adherence clubs (Objective 2) | Proportion of patients eligible for participation in an adherence club who receive all medications within the first four months after club eligibility (S) and the proportion virally suppressed (< 400 copies/ml^3^) at twelve months after club eligibility (L). | Proportion of patients consistently participating in club  Demographic and clinical characteristics of patients who do and do not achieve primary outcomes. |
| Decentralized medication delivery (Objective 3) | Proportion of patients eligible for decentralized medication delivery who receive all medications within the first three (S) months after delivery eligibility and viral suppression (< 400 copies/ml^3^) twelve months after delivery eligibility (L). | Proportion of patients consistently receiving medications  Demographic and clinical characteristics of patients who do and do not achieve primary outcomes. |
| Enhanced adherence counseling (Objective 4) | Proportion of patients with an elevated viral load who are alive, retained in care and resuppress their viral load (< 400copies/ml^3^) within three (S) and twelve months (L) of eligibility for enhanced adherence counseling. | Demographic and clinical characteristics of patients who do and do not achieve primary outcomes. |
| Early tracing of patients lost to follow up (Objective 5) | Proportion of patients eligible for early patient tracing who return to care within three (S) and twelve (L) months of eligibility. | Proportion of patients reached by tracers  Number of tracing attempts required; proportion of patients retained in care for at least one additional routine visit after tracing  Demographic and clinical characteristics of patients who do and do not achieve primary outcomes. |
| Overall impact (Objective 6) | Proportion of population in need at each clinic who achieve the short term primary outcomes defined above. | Proportion of population in need at each clinic who achieve the long term primary outcomes defined above. |
| Cost  (Objective 7) | Average cost per patient receiving an adherence intervention | Average cost per primary outcome achieved; average cost per 1000 patients receiving the observed mix of interventions |
| TB, hypertension, and diabetes (Objective 8) | For each condition, proportion of patients eligible for treatment who have 80% visit compliance in the first three months after diagnosis (S) and who achieve disease control at the six-month visit after diagnosis (L) as indicated in “Primary Care 101,” the NDOH’s guide for primary health clinic services[15]. The six-month visit will be represented by the visit closest to six months within the window of 5-8 months after diagnosis. The disease control indicators to be measured, with page references for Primary Care 101, are:  TB: cured or treatment completed indicated as the patient’s status at 6 months (page 57)  Hypertension: blood pressure controlled at 6-month visit, with control defined as < 140/90 (or 120/70–140/80 if diabetes, or <130/80 if CVD, heart failure or kidney disease) (page 74)  Diabetes: random glucose < 8 or HbA1c ≤ 7% at 6 month visit (page 71) | Among patients screened, prevalence of pre-diabetes elevated blood sugar (defined by Primary Care 101 as random glucose between 7.8 and 11) and pre-hypertension elevated blood pressure that require monitoring  Proportion of patients diagnosed with pre-diabetes or pre-hypertension who a) progress to diabetes and hypertension; or b) remain in care and receive appropriate monitoring for their condition over 12 months  Prevalence of diabetes, hypertension and TB among patients screened  Proportion of diagnosed patients initiated on appropriate treatment  Proportion of patients on treatment retained in care at 12 months. Loss to follow up will be defined as being 30 days late for a scheduled appointment.  Demographic and clinical characteristics of patients who do and do not achieve primary outcomes. |

For all outcomes under Objectives 1-5 and 8, retention in care will be defined as (1-% attrition), with attrition calculated as the sum of reported deaths, loss to follow up, and reported transfers to other facilities. Retention will thus be interpreted as “retained in care at facility,” since the outcomes of patients who transfer will not be known. Where national identification numbers are available, the national death registry will be searched to locate unreported deaths. Loss to follow up will be defined as failure to attend the clinic within 90 days of a scheduled appointment, as stated in the Adherence Guidelines (Table 7 page 49).

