## **a. Fast Track ART Initiation Counseling**

Fast track initiation seeks to reduce attrition from chronic care by speeding up the process of treatment initiation for patients who are eligible for treatment and thereby increasing the proportion of treatment-eligible patients who start treatment promptly. For HIV, the goal is to reduce the total number of visits that patients need to complete in order to start treatment and allow patients to initiate treatment over the course of two clinic visits within one week of confirming ART eligibility, with additional counseling provided in the first two routine visits after treatment initiation. The intervention includes a detailed curriculum for the counseling sessions, and providers work with patients to create an individualized adherence plan and ensure post-initiation adherence support[12].

| *Primary outcome:* | Proportion of ART-eligible patients who initiate ART (obtain their first supply of ARV medications) within 30 days of determination of treatment eligibility |
| --- | --- |
| *Eligibility:* | All non-pregnant adult patients who are eligible for ART according to national guidelines (CD4 cell count ≤ 500 or Stage 3 or 4 condition) |
| *Sample size:* | 720 (360 per arm; 30 per cluster) |
| *Data sources:* | HIV counseling and testing (HCT) and CD4 count registers; adherence plans; Tier.Net (South Africa’s national HIV patient care database); counselling registers and other registers or records that document services received prior to ART initiation (including patient record) |

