## **b. Inclusion and Exclusion Criteria**

For Objectives 1-5 and Objective 8, we will enroll a specific cohort of patients. These will be numbered in accordance with the objective number for Objectives 1-5; for Objective 8, the cohort will be called the “TBHD cohort”, in reference to tuberculosis, hypertension, and diabetes. This TBHD cohort will be made up of patients who have been screened for TBHD (50%) and patients who are newly diagnosed with TB, hypertension or diabetes (50%). For all cohorts, inclusion and exclusion criteria are as shown below. For Objectives 1-5, these criteria follow the December 2014 national guidelines for HIV care and ART[10] and November 2015 National Adherence Guidelines for Chronic Disease (HIV, TB and NCDs) [11].

*Cohorts 1-5 and TBHD cohort inclusion criteria*

- ≥ 18 years old
- Meet the inclusion criteria for one or more of Cohorts 1-8

*Cohorts 1-5 and TBHD cohort exclusion criteria*

- Not resident in the facility’s catchment area
- Recorded intention to transfer care to a different facility within 12 months
- Pregnant and eligible for PMTCT

*Objective 1/Cohort 1 inclusion criteria (Patients newly eligible for ART—fast track treatment initiation)*

- Determined to be eligible to start ART under prevailing national guidelines (CD4 count < 500, WHO Stage 3 or 4 condition, TB, cryptococcal meningitis)

*Objectives 2 and 3/Cohorts 2 and 3 inclusion criteria (Patients stable on ART—adherence clubs or decentralized medication delivery)*

- On same ART treatment regimen for at least 12 months
- Most recent viral load taken in past 6 months
- Two consecutive viral loads undetectable (<400 copies/ml^3^)

*Objective 4/Cohort 4 inclusion criteria (Patients on ART with poor adherence—enhanced adherence counseling)*

- On first line ART for at least 6 months
- Poor adherence as indicated by an elevated viral load (>400 copies/ml^3^)

*Objective 5/Cohort 5 inclusion criteria (Patients lost from ART programs—early patient tracing)*

- Initiated ART
- Fail to return for a scheduled appointment within 5 to 90 days from their appointment date

*Objective 8/TBHD cohort inclusion criteria (Tuberculosis, hypertension, and diabetes patients)*

- Screened for or diagnosed with for TB or hypertension within the last month, or diabetes within last 6 months

*Objective 8/TBHD cohort exclusion criteria (Tuberculosis, hypertension, and diabetes patients)*

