- Clinic file, register, and card numbers (assigned by the clinic)*
- National ID number*
- Name*
- Date of birth*
- Weight and height or BMI
- Sex
- Age in years
- Marital status if recorded
- Employment status if recorded
- Education level if recorded
- Smoking and alcohol use if recorded

*To be used to link electronic and paper-based records pertaining to individual patients. Many clinics use name or initials and date of birth to create a clinic record number.

*Objectives 1-5, HIV cohorts:*

- Date of positive HIV test (if available)
- Dates of all clinic visits (including pre-ART and after ART initiation)
- Primary purpose of all clinic visits (e.g. HIV test, CD4 count, counselling, ARV dispensing, ART monitoring, etc.)
- Dates of next scheduled clinic visits (dates patients are expected to return to clinic)
- Date treatment eligibility determined, if reported
- Date and result of CD4 count indicating treatment eligibility (baseline)
- WHO stage and clinical conditions
- Date and result of TB symptom screen
- Date, type, and result of TB test
- Date TB treatment initiated, if relevant*
- Date and result of cryptococcal meningitis test
- Date cryptococcal meningitis treatment initiated, if relevant*
- Date ART initiated (first dose of medications dispensed)
- First-line regimen prescribed
- Any changes to first line regimens and dates of changes
- Dates and results of all viral load tests
- Dates and results of all other laboratory investigations
- All completed fields in Adherence Plan, if entry into an electronic database is feasible (attached)
- Dates of eligibility for receiving interventions
- Dates of participation in intervention activities or receipt of intervention services (e.g. Adherence Club visits, tracing attempts, counseling sessions)
- Dates interventions received if documented

*These conditions require a delay in ART initiation and are thus important in evaluating Cohort 1.

*Objective 8, TB, hypertension, and diabetes cohort:*

- All fields in the Chronic Patient Record (attached). (Note: These fields may be recorded by the sites in other formats, such as registers or patient files, if the Chronic Patient Record is not yet in use; we will extract them from whatever source documents are available.)
- Dates and results of screening tests
- Dates and results of all laboratory investigations
- Dates of all clinic visits
- Prescribed medications
- Primary purpose of all clinic visits

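### Cohort 1 admits patients whose ART start the protocol says must be delayed, but its 30-day and one-week outcomes make no allowance for them

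*Protocol*

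**What the plan says.** **Entry.** Protocol section 8b defines Cohort 1 as patients "Determined to be eligible to start ART under prevailing national guidelines (CD4 count < 500, WHO Stage 3 or 4 condition, TB, cryptococcal meningitis"). The exclusions common to all cohorts cover residence outside the catchment area, planned transfer, and "Pregnant and eligible for PMTCT". None removes patients with TB or cryptococcal meningitis. The shorter eligibility line in section 4a does not name the two conditions, but does not exclude them either.

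**Delay.** The field list in section 9b includes the TB treatment start date and "Date cryptococcal meningitis treatment initiated, if relevant". Both carry a footnote: "These conditions require a delay in ART initiation and are thus important in evaluating Cohort 1". The length of the delay is not given.

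**Outcome.** Section 4a defines the primary outcome as "Proportion of ART-eligible patients who initiate ART (obtain their first supply of ARV medications) within 30 days of determination of treatment eligibility". Table 3 in section 10a repeats the 30-day window as "Proportion of patients who initiate ART within 30 days of becoming ART eligible (S"), and adds a one-week secondary outcome. Neither place has an exception, a separate clock or a separate stratum. For Objective 1, Table 3 uses TB only to describe who did and did not reach the outcome, and does not name cryptococcal meningitis.

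**Analysis.** Section 10c fixes the relative risk as the effect measure. It adjusts for covariates only if an imbalance is found, and stratifies by an open list of baseline characteristics that does not name these conditions.

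**The concern.** The protocol calls the two conditions important for evaluating Cohort 1 and collects their dates, yet fixes a primary outcome that ignores them. A patient whose start is held back past day 30 because of the condition gets the same score as a patient who never returned. The intervention targets the counselling pathway, with a start over two visits within a week (section 4a). It is not described as removing a delay that the patient's condition requires.

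At stake are the proportions reported for each arm, the absolute difference, and the power to detect it. The one-week outcome is the more exposed, since any required delay longer than seven days is a certain miss. The effect also carries further: Objective 6 builds on the short-term primary outcomes, and Objective 7 includes a cost per primary outcome achieved.

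**Working it through.** **Inputs from the protocol.** 60% versus 75% starting within 30 days, and 30 patients in each of 24 clinics, 720 in all (Table 4). Coefficient of variation 0.1, 80% power, alpha 0.05 (section 10b).

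**Assumptions.** Alpha is two-sided. A share *p* of Cohort 1 must wait beyond 30 days and so misses the window in either arm. The 60% and 75% apply to everyone else. The protocol does not give *p*; the range shown is 5% to 20%.

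**The plan's own figure.** The standard formula for cluster trials with a between-cluster coefficient of variation *k*, with *c* clinics per arm and *m* patients per clinic, is

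*c* = 1 + (z_α/2 + z_β)² × V / (p1 − p0)², where V = p0(1 − p0)/m + p1(1 − p1)/m + k²(p0² + p1²).

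With *c* = 12, *k* = 0.1 and 80% power this needs 19.2 patients per clinic (22.0 in the matched form, which adds 2 instead of 1). The stated 30 is therefore not reproduced and is larger than its inputs require. At *m* = 30:

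- V = 0.24/30 + 0.1875/30 + 0.01 × (0.36 + 0.5625) = 0.02348
- √(11 × 0.0225/0.02348) − 1.96 = 1.29, so power is about 90%

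That 90% is the starting point below. The point does not depend on reproducing the 30.

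**Equal shares in both arms.** Observed rate = (1 − *p*) × planned rate. In the restricted analysis the rates stay at 60% and 75%, and *m* becomes 30 × (1 − *p*).

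| *p* | Comparison | Intervention | Difference (points) | RR | Power, all patients | Power, restricted |
|---|---|---|---|---|---|---|
| 0% | 60.0% | 75.0% | 15.0 | 1.25 | 90% | 90% |
| 5% | 57.0% | 71.3% | 14.3 | 1.25 | 87% | 89% |
| 10% | 54.0% | 67.5% | 13.5 | 1.25 | 84% | 88% |
| 15% | 51.0% | 63.8% | 12.8 | 1.25 | 80% | 87% |
| 20% | 48.0% | 60.0% | 12.0 | 1.25 | 76% | 86% |

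Table 4 does not make clear whether 30 already contains the 20% increase for ineligible patients. If it does (30/1.2 = 25 per clinic), all-patient power is 87% at *p* = 0, then 83% at 5%, 79% at 10% and 70% at 20%.

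**Shorter delays.** If half of the affected patients still start in time, equally in both arms, the difference shrinks by the same amount and the RR moves slightly, to 1.24 at *p* = 5% and 1.21 at *p* = 20%.

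**Unequal shares by chance.**

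- 15% in intervention and 10% in comparison clinics: 0.85 × 75 = 63.75% versus 0.90 × 60 = 54.0%, RR 1.18
- The reverse: 0.90 × 75 = 67.5% versus 0.85 × 60 = 51.0%, RR 1.32

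**The case against.** Four arguments on the other side have weight.

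- **The delay may be short.** A reader might infer that correct care is bound to count as failure at 30 days. The documents do not support that. The footnote speaks of a delay without giving its length, and a delay under 30 days uses up part of the window without forcing a miss. The number of patients affected cannot be computed from the protocol.
- **The effect measure is the relative risk.** A reader might infer that these patients dilute or bias it. With equal shares, and all affected patients missing day 30, it is unchanged at 1.25. Randomising the clinics makes the expected shares equal, so a 15% versus 10% split is random error, not systematic bias. Section 10c also allows adjustment for imbalances that are detected. What remains is the extra noise, the smaller absolute difference and the lost power. Adjustment after the fact does not change how a delayed start is scored.
- **The 60% may already include such patients.** Table 4 takes it from ART-eligible patients under standard care and does not say whether delayed patients were left out. If they were counted, the planning rates partly absorb the loss. Even if they were not, power at 30 per clinic drops below 80% only when *p* exceeds about 15%.
- **Replacing the primary denominator is debatable.** Section 4 aims to cover each clinic's whole patient population, and the diagnoses are recorded by staff after the clinics are randomised. Nor can the 20% allowance be assumed to pay for a smaller denominator: it is for ineligible patients, and these patients are eligible.

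A statistical analysis plan, not at hand, may use the collected dates. It would still start from an outcome that the protocol has fixed without any allowance.

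**Conclusion.** The mismatch is real and lies within the protocol: entry with TB or cryptococcal meningitis, a stated required delay, and fixed 30-day and one-week clocks with no provision for it. On the assumptions above, with 5% to 20% affected, the cost is a difference of 14.3 to 12.0 points instead of 15, and power of 87% to 76% instead of about 90%. The relative risk is noisier but not systematically shifted. The size is uncertain because the delay length, the share affected and the make-up of the 60% baseline are all unstated. The effect on the one-week outcome is probably larger, but cannot be sized because the protocol gives no planning rates for it. This supports prespecified additional analyses. It does not show that the all-patient primary outcome is invalid or has to be replaced.

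**What to change.** Reconcile sections 8b, 9b and 10a (with 4a), without taking a position on when ART should start. Then prespecify, identically in both arms:

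1. An analysis of the 30-day and one-week outcomes in Cohort 1 patients with no TB or cryptococcal meningitis recorded on or before the eligibility date.
2. Patients with either condition reported as a separate stratum.
3. Baseline TB or cryptococcal meningitis status as an adjustment covariate in the all-patient model, in place of adjusting only when an imbalance is detected. If almost nobody in that stratum starts within the window, the covariate term may not be estimable; the restricted analysis then carries the comparison.
4. The all-patient result alongside, and all patients kept in the nine-month outcome.

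**Cost.** This is a change of wording, and the fields are already on the collection list. The restricted analysis has a somewhat smaller denominator, with power of about 89% to 86% for *p* of 5% to 20%. It relies on routinely recorded diagnoses, so the recording rates of both conditions should be compared between arms. Patients diagnosed after the eligibility date stay in the restricted set and should be counted and reported.

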## **b. Sample Size**

Table 4 shows the sample size that is required to detect meaningful differences for Objectives 1-5 and for estimating precise rates for Objective 8. Each sample size is determined to measure our short term outcome for the objective. For Objectives 1-5, all calculations assume a site-clustered design with the clinic as the cluster; 24 clusters evenly split (randomized) between intervention and comparison groups; a coefficient of variation of 0.1, 80% power; and an alpha of 0.05.

**Table 4. Sample sizes for each objective**

| **Objective** | **Sample Size** | **Rationale** |
| --- | --- | --- |
| Objective 1—Fast Track ART Initiation Counseling | 720 patients | The RapIT study of rapid ART initiation, conducted at a well-managed PHC in Gauteng Province, found that about 60% of ART-eligible patients initiated under standard care within 30 days. Conservatively assuming 60% initiation without the intervention and 75% with the intervention, 30 subjects in each of the 24 clusters for 720 total subjects will be required to detect a difference of 15%. We have increased this by 20% to account for ineligible patients. |
| Objective 2—Adherence Clubs | 576 patients | Data from Themba Lethu Clinic show that about 80% of patients made all of their medication pickups over a three month period. It is anticipated that 24 subjects per clinic for a total of 576 patients will be needed to detect a difference of 15%. We have increased this by 20% to account for ineligible patients. |
| Objective 3—Decentralized Medication Delivery | 576 patients | Data from Themba Lethu Clinic show about 80% of patients made all of their medication pickups over a three month period. It is anticipated that 24 subjects per clinic for a total of 576 patients will be needed to detect a difference of 15%. We have increased this by 20% to account for ineligible patients. |
| Objective 4—Enhanced Adherence Counseling | 1008 patients | Data from KZN indicate that 52% of patients with a detectable viral load re-suppress after one session. It is anticipated that 42 subjects per clinic for a total of 1008 patients will be needed to detect a difference of 15%. We have increased this by 20% to account for ineligible patients. |
| Objective 5—Early tracing of patients lost to follow up | 576 patients | Data from various Right to Care clinics suggest that the proportion of patients who are lost from care who return with no or little intervention is low, between 20-35%. It is anticipated that 24 subjects per clinic for a total of 576 patients will be needed to detect a difference of 15% assuming a baseline of 30% loss to follow up without intervention. We have increased this by 20% to account for ineligible patients. |
| Objective 6—overall impact | 0 patients | No additional subjects will be enrolled for the overall impact analysis, which will rely on data from Cohorts 1-5. |
| Objective 7—Cost | 0 patients | No additional subjects will be enrolled for the cost estimates, which will rely on data from Cohorts 1-5. |
| Objective 8—TB, hypertension, and diabetes | 4800 patients | Because Objective 8 is descriptive in nature, no specific sample size will be targeted. We will instead include up to the first 100 patients per site who are eligible for screening and 100 patients who are recently diagnosed and treated for TB, hypertension and/or diabetes, for a total of 4800. (We note that some patients eligible for the TBHD cohort will also be eligible for Cohorts 1-5, due to co-morbidities with HIV. These patients will be co-enrolled in both cohorts.) |

Total enrollment will thus be 2,880 in cohorts 1-5 and 4,800 in the TBHD cohort, for a total sample size of 6,680.

Due to the size criterion for study site selection, with all clinics included in the evaluation having at least 1,000 current ART patients, we anticipate being able to enroll the target sample sizes for all cohorts during a 6-month enrollment period. Enrollment for Cohorts 4 and 5 and 8 may take longer than this depending on baseline rates of viral suppression and visit compliance at the selected clinics and number of newly screened and diagnosed TBHD patients.

We will monitor the data for Cohorts 1-5 closely and amend the protocol to increase the sample size for these cohorts if needed to ensure adequate analytic power.

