# SUMMARY

The South Africa National Department of Health (NDOH) intends to launch its newly developed National Adherence Guidelines for Chronic Diseases (HIV, TB and NCDs) throughout South Africa in the coming year. Early implementation of the “minimum package” of interventions described in the Adherence Guidelines for HIV patients will take place at 12 primary health clinics and community health centres in four provinces starting in July 2015. To maximize the learning potential of this early implementation stage, NDOH will match the intervention clinics with 12 comparison clinics and randomly allocate intervention or comparison status within the pairs of clinics. This will allow the outcomes of the interventions to be evaluated using a cluster-randomized design and generate data on the costs of implementation and the potential need for adherence support for the other diseases addressed in the guidelines (tuberculosis, hypertension, and diabetes). This protocol is for the evaluation, which will generate information on the effectiveness of minimum package interventions and help improve the design, implementation, and budgeting of the guidelines.

We will assess the effectiveness of five interventions in the minimum package: 1) Fast track initiation counseling for patients eligible for antiretroviral therapy; 2) Enhanced adherence counseling for unstable patients on HIV treatment; 3) adherence clubs for stable patients on HIV treatment; 4) decentralized medication delivery for stable patients on HIV treatment; and 5) early tracing of all patients who miss an appointment by two weeks. We will also estimate for each study site an overall “adherence guideline impact” to provide an indication of the effectiveness of the package as a whole.

In addition, we will estimate the cost of each of the interventions listed above compared to standard of care. Finally, we will describe the cascade of care for tuberculosis, hypertension, and diabetes, three other chronic diseases for which little information currently exists. To evaluate these interventions we will work with the National Department of Health (which will implement the interventions) to randomize 24 clinics in 4 provinces 1:1 to receive the interventions or continue standard of care. All evaluations will use data routinely collected by the clinics, with no study interaction with subjects. A total of 8,256 patients will be enrolled and followed for up to 20 months to estimate short- and long-term outcomes.

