# EVALUATION OF INTERVENTION EFFECTIVENESS (OBJECTIVES 1-5)

To achieve the first five objectives, we will test the effectiveness of five interventions included in the minimum package of adherence interventions using routinely collected data only. The interventions have been developed by the NDOH and will be implemented by the public sector clinics using their own staff and resources. Those interventions included in the evaluation were selected as having outcomes that could be assessed in a relatively short period of time, so that results can be used to refine the national guidelines and implementation. Below we detail each of the interventions and the populations we will use to evaluate the interventions.

We will use a matched cluster randomized design to evaluate the impact of each of the selected interventions. The National Department of Health, in consultation with the study team, will develop a short list of candidate primary health care clinics where early implementation of the package can occur. This short list will include proposed matched pairs of facilities which will be randomized to either implement the minimum package or not. Clinics will be matched on characteristics that are likely to affect study outcomes (patient volume, urban/rural location, current HIV viral suppression rate).

Because the interventions will be implemented clinic-wide and the evaluation will rely on routinely collected data only, we will include the entire patient population at each study site. All non-pregnant adult patients seeking HIV-related services at the study sites and eligible to receive one of the adherence interventions during the enrollment period will be included in the study through use of their clinic data. There will be no direct interaction with study subjects. Data will be collected from existing, routinely completed patient records, including clinic files, registers, cards, and databases. No additional data fields, beyond what are currently mandated under government guidelines, will be collected for the study. We assume that all study sites will follow the current guidelines for HIV care and treatment, dated December 2014[10] and the Primary Care 101 guide for TB, HIV, diabetes and hypertension care and treatment, dated 2013/14[15] as well as comply with the National Health Act of 2003.

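### The total enrolment of 6,680 contradicts Table 4, the Summary and its own addends, and Objective 4's 42 per clinic does not follow from the stated inputs

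*Protocol*

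**What the plan says.** The Summary states: "A total of 8,256 patients will be enrolled and followed for up to 20 months". The paragraph after Table 4 in section 10.b states: "Total enrollment will thus be 2,880 in cohorts 1-5 and 4,800 in the TBHD cohort, for a total sample size of 6,680".

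Table 4 lists 720, 576, 576, 1,008 and 576 patients for Objectives 1 to 5, and up to 4,800 for Objective 8. The boxes in sections 4.a to 4.e give the same five totals, with 30, 24, 24, 42 and 24 per cluster.

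Section 10.b gives the common inputs for Objectives 1-5: "24 clusters evenly split (randomized) between intervention and comparison groups" and "a coefficient of variation of 0.1, 80% power; and an alpha of 0.05". For Objective 1, Table 4 says that "30 subjects in each of the 24 clusters for 720 total subjects will be required to detect a difference of 15" percentage points, and then that this was raised by 20% for ineligible patients. The other four rows have the same structure. Section 4 describes the design as matched: "We will use a matched cluster randomized design to evaluate the impact of each of the selected interventions". No sample size formula is named, and the text does not say whether the matching entered the calculation.

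**The concern.** Three things need settling.

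- **The total.** Two totals are printed for one study, and one of them is not the sum of its own parts.
- **The 20%.** Read literally, each Table 4 row says that the listed number is what detection requires and that an increase then follows. A reader cannot tell whether 720, for example, is the evaluable requirement or the inflated enrolment target.
- **Objective 4.** Its rates (52% against 67%) are statistically much like Objective 1's (60% against 75%), yet it has 42 per clinic against 30.

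Section 9.d has enrolment run until the targets are met, and section 10.b promises to raise the size of Cohorts 1-5 if needed to protect power. That second decision needs a clear evaluable number per cohort and a calculation that can be repeated.

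**Working it through.** **Totals**

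- The sentence's own addends: 2,880 + 4,800 = 7,680, which is 1,000 more than the printed 6,680.
- Table 4, Cohorts 1-5: 720 + 576 + 576 + 1,008 + 576 = 3,456, which is 576 more than 2,880.
- With Objective 8, 24 × (100 + 100) = 4,800: 3,456 + 4,800 = 8,256. This reproduces the Summary and is 1,576 more than 6,680.

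**Is the 20% already included?**

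Dividing the listed per-clinic numbers by 1.2 gives 25, 20, 20, 35 and 20, all whole multiples of 5. Sections 4.a to 4.e and the 8,256 total also use the listed numbers with nothing added. Both facts suggest that the 20% is included. On the literal reading, Cohorts 1-5 would need 3,456 × 1.2 ≈ 4,147, a figure that appears nowhere.

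**Per-clinic sizes**

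Inputs from section 10.b and Table 4: c = 12 clinics per arm, k = 0.1, 80% power, alpha 0.05 (taken as two-sided, since sidedness is not stated), and a difference of 0.15. The standard formula for cluster trials with a between-cluster CV is

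c = a + (1.96 + 0.842)² × [p0(1−p0)/m + p1(1−p1)/m + k²(p0² + p1²)] / (p1 − p0)²

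where a = 1 for unmatched and a = 2 for matched clusters. Solved for m:

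m = [p0(1−p0) + p1(1−p1)] / [(c − a)(p1 − p0)²/7.849 − k²(p0² + p1²)]

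Objective 4, matched: 0.4707 / (10 × 0.0225/7.849 − 0.00719) = 0.4707/0.02147 = 21.9.
Objective 4, unmatched: 0.4707 / (11 × 0.0225/7.849 − 0.00719) = 0.4707/0.02434 = 19.3.

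| Objective | Rates | m, a = 1 | m, a = 2 | a = 2, rounded up to next 5, × 1.2 | Table 4 |
|---|---|---|---|---|---|
| 1 | 60% vs 75% | 19.2 | 22.0 | 30 | 30 |
| 2, 3 | 80% vs 95% | 12.9 | 15.7 | 24 | 24 |
| 4 | 52% vs 67% | 19.3 | 21.9 | **30** | **42** |
| 5 | 30% vs 45% | 16.0 | 17.8 | 24 | 24 |

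A matched calculation with a continuity correction and division by 0.8 also gives 30, 24, 24, 30 and 24. Among the two-sided, 80%-power variants tried with 12 clinics per arm, none put Objective 4 above 30.

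**What 42 would correspond to**

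Take 42/1.2 = 35 evaluable per clinic. The variance term is 0.4707/35 + 0.00719 = 0.02064.

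- Power, a = 2: 0.15/√(0.02064/10) = 3.30, and 3.30 − 1.96 = 1.34, so 91%.
- Power, a = 1: 0.15/√(0.02064/11) = 3.46, and 3.46 − 1.96 = 1.50, so 93%.
- CV giving exactly 80% power: k² = (0.02867 − 0.01345)/0.7193, so k ≈ 0.145 (a = 2); k² = (0.03153 − 0.01345)/0.7193, so k ≈ 0.16 (a = 1).
- Alternatively, keeping CV 0.1, a detectable difference of about 12 to 13 points.

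**Power of the other rows at CV 0.1**

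With 25, 20, 20 and 20 per clinic, Objectives 1, 2, 3 and 5 have 83%, 84%, 84% and 84% (a = 2), or 87% each (a = 1). Objective 5's baseline is worded as loss to follow-up. Read as 70% against 85%, its power at 20 per clinic is 79.5% (a = 2) or 83% (a = 1).

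**The case against.** The strongest reply is that nothing operational depends on the faulty sentence. Enrolment runs by cohort, and Table 4 and sections 4.a to 4.e agree on every cohort total and every per-clinic number. That stands, and it is why the correction is only to the text. It does not make the sentence right: the headline size still contradicts the Summary and its own table. Co-enrolment of patients in the Objective 8 cohort does not rescue 6,680 either. The protocol allows it but subtracts nothing for it.

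Some stronger readings are tempting but unsupported:

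- **That Table 4 as a whole fails to follow from its inputs.** The unrounded formula values times 1.2 do fall below the table. But the protocol states no formula or rounding rule, and a matched calculation rounded up to the next 5 reproduces Objectives 1, 2, 3 and 5 exactly. That route is inferred, but it shows that those rows are compatible with the inputs.
- **That the trial is underpowered or conceals its dependence on the CV.** The CV of 0.1 is stated openly. Power does fall at larger values, but the protocol gives no ground for any particular one, and it already plans to monitor and enlarge the cohorts.
- **That 2,880 is the total before inflation.** 3,456/1.2 = 2,880, but 3,456 − 576 = 2,880 as well, which would be one 576-patient cohort left out. The origin is a question for the authors.

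**Conclusion.** The total in section 10.b is wrong; this rests on addition alone. The figure consistent with Table 4, sections 4.a to 4.e and the Summary is 8,256, made up of 3,456 in Cohorts 1-5 and up to 4,800 for Objective 8. The status of the 20% is ambiguous as worded, although the surrounding figures point to its being included.

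Objective 4's 42 per clinic does not follow from CV 0.1, 80% power and 15 points. About 19 (unmatched) to 22 (matched) would be needed before inflation, against 35 if the 20% is included. The row is larger than needed, at about 91-93% power, so either a different CV or difference was used or the row is wrong. This conclusion assumes two-sided alpha, the standard CV formula, and 52% against 67%. At the stated CV no row is materially underpowered; the lowest value found is 79.5%, for Objective 5 under its less favourable reading with matching.

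**What to change.** 1. In section 10.b, replace the sentence with 3,456 in Cohorts 1-5 plus 4,800 for Objective 8, 8,256 in all. Call these cohort enrolments rather than unique patients, here and in the Summary, because co-enrolment is allowed.
2. In Table 4, confirm that the listed numbers already include the 20%, and add the evaluable number required for each row from the authors' own calculation. Dividing by 1.2 should not stand in for that calculation.
3. Name the formula, say whether the matching was used, and state the sidedness of alpha.
4. For Objective 4, give the CV or difference actually used, or restate the row's power at the stated inputs.

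The cost is a text and table correction. Cohort targets and enrolment stay as they are.
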